#### Preprocessing of MRIs

sMRI data will be processed using an optimized SPM12 (Statistical Parametric Mapping, Wellcome Trust Center for Neuroimaging, London, United Kingdom) procedure validated in our previous study (15) to generate the gray matter (GM) and white matter (WM) density maps (for Aim3). With the notion that our scanner delivers 5 pulses without image acquisition for signal stabilization, standard preprocessing of fMRI data will be used, including motion, distortion, and slice timing corrections, normalization to standard space, and motion scrubbing and physiological noise removal using the RETROICOR approach (32). Pre-processing of fMRS will include phase-, shift-, and eddy current correction and removal of the first fMRS measurement for each condition. Two consecutive spectra in each condition will be averaged to increase the signal-to-noise ratio. Pre-processing of DTI will include correction of image distortions from eddy currents and detection and replacement of outliers due to the head and cardiac pulsatile motion. The HRF features (for Aim 1 and Aim 3) will be modeled using sHRF toolkit developed in our previous study (33) based on tfMRI. The sample entropy (SampEn) map of BOLD signal changes (for Aim 3) will be calculated as in our previous study (10) based on tfMRI. The fractional amplitude of low-frequency fluctuation (fALFF) map of task residue BOLD signal changes (for Aim 3) will be calculated as the power within the low-frequency range (0.01–0.1Hz) divided by the total power in the entire detectable frequency range (34) after removing task-related activity with the general linear modeling (35). Resting glutamate levels and dynamic glutamate changes in task conditions (for Aim 2) will be calculated using ‘LCModel' (version 6.3) with a simulated basis set for prior knowledge (36). The apparent diffusion coefficient and fractional anisotropy maps (for Aim 3) will be calculated using the FMRIB Software Library (FSL) based on diffusion MRI data. The RRF (for Aim 1 and 3) will be modeled similarly to our previous study (33) with an RRF which is slower than neuronally-induced BOLD signal changes (37) based on the breath-holding tfMRI.

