#### Actigraphy

Participants will be given a GT3X-BT device with a heart rate monitor to wear 7 days before the MRI. The heart rate monitor is to be worn for 24 h. After the MRI scan, participants will be given another GT3X-BT device to wear for 7 days with a 24-h heart rate monitor to be worn on the next morning of the MRI scan. We will collect actigraphy data before and after the MRI scanning (i) to obtain a robust estimations of activity levels, sleep qualities, and heart rate variabilities and (ii) to investigate sleep quality and heart rate variability changes after a moderate exertion (MRI scanning) in ME/CFS.

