### Data analysis plan

The measured variables will firstly be tested for normal distribution. Equivalent non-parametric methods will be used if any variable does not exhibit a normal distribution. The activity measure, body mass index, age, depression, and anxiety will be included as covariates for all statistical analyses. The false discovery rate (FDR) will be used to correct for multiple comparisons.

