#### Group difference in hemodynamic response function (HRF) (Aim 1)

The HRF features will be compared using one-way analysis of covariance (ANCOVA) among the four groups. The respiration response function (RRF) will be modeled in the breath-holding tfMRI data. This will enable us to disentangle non-neuronally-induced cerebrovascular reactivity from the neurovascular coupling effects. The RRF will be summarized similarly to the HRF by amplitude (*H*), time to peak (*T*), onset (*O*), and width (*W*). The RRF features at the same brain location will be used as a covariate in the HRF ANCOVA analysis to exclude confounding cerebrovascular reactivity (e.g., RRF-*H* as a covariate for HRF-*H* comparison, etc.,). Group differences in each RRF feature will also be tested using ANCOVA among the four groups. The bivariate correlation will be tested between the HRF/RRF features and the health scores. Additionally, the extent to which these correlated features explain variance in the health scores after accounting for all other variables will be evaluated using hierarchical regression.

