**Figure 4 F4:**
[figure not shown]
Power analysis. The theoretic sample size was determined by the sensitivity value (effect size = 0.25) that further decreasing the effect size from 0.25 to 0.2 requires appreciably increasing the sample size from 251 to 390. The sample size assumes that 87% of data are valid (*N* = 251/0.87 ~ 288). Invalid data include MRI images with excessive motions and new conditions found after completion of the study, and the percentage was estimated empirically. The analysis of covariance (ANCOVA) will be used to determine the mean difference among four groups with 5 covariates of age, gender, activity levels, body mass index, depression, and anxiety. We assumed both type I and II errors of 0.05.

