### Controlling confounding factors

ME/CFS is an illness currently defined by consensus criteria and questionnaires completed by patients. Thus, there is a risk of an ill-defined ME/CFS patient cohort. The proposed study will mitigate this problem by following CCC ME/CFS criteria and diagnosis agreed by two experienced clinicians ([name] and [name]).

Patients with ME/CFS or fibromyalgia may have ongoing medications, which is logistically unavoidable for the study. We mitigate this risk by following steps. (1) Individuals using marijuana or substance were excluded because their known alteration of brain structure and function. (2) Each medication will be determined individually by agreement of investigators ([name], [name] and [name]) on whether it affects the NVC. We include individuals on medication that does not affect the NVC. (3) Two clinicians ([name] and [name]) will assess individuals on medication affecting the NVC to determine if it is safe to stop medication for 3 weeks. Individuals considered safe to stop medication will further seek professional opinions from their caring physicians and then stop medication 2 weeks before and 1 week after MRI. We will exclude individuals who are at risk to stop medication affecting the NVC.

Both ME/CFS and fibromyalgia predominantly affect females (39). Thus, we may recruit more females than males. Indeed, our current sample includes 82% female and 18% male in all groups, including HCs. This unequal sex ratio risk cannot be avoided because of diseases' inherent features. We will include sex as a covariate in all statistical analyses.

This project started when the severe acute respiratory syndrome coronavirus 2 (SARS-CoV-2) occurred before the long Covid (post-acute sequelae of SARS-CoV-2 infection) was recognized. We decided to keep the study protocol and follow the CCC ME/CFS criteria while considering SAR-CoV-2 as an infection similar to other infections that occurred before the manifestation of ME/CFS.

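### The covariates stated for all group analyses include no head-motion summary, so residual motion that differs by group would go unadjusted in the fMRI comparisons and could enter the neuromarker

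*Protocol article*

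**What the plan says.** Motion is handled at image level in three places.

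- fMRI (Preprocessing of MRIs): "standard preprocessing of fMRI data will be used, including motion, distortion, and slice timing corrections", and further along the same list "motion scrubbing and physiological noise removal using the RETROICOR approach".
- DTI (same section): "detection and replacement of outliers due to the head and cardiac pulsatile motion".
- Exclusion (Figure 4 legend): "Invalid data include MRI images with excessive motions and new conditions found after completion of the study". Such data fall within the 13% allowance that takes the sample size from 251 to 288.

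The group-level covariates are stated separately.

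- Data analysis plan: "The activity measure, body mass index, age, depression, and anxiety will be included as covariates for all statistical analyses".
- Controlling confounding factors, and the abstract, add sex: "We will include sex as a covariate in all statistical analyses".
- The Aim 1 section adds one imaging covariate for HRF: "The RRF features at the same brain location will be used as a covariate in the HRF ANCOVA analysis".
- The Figure 4 legend bases the power analysis on age, gender, activity, body mass index, depression and anxiety.

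Preprocessing of MRIs assigns HRF and RRF features to Aims 1 and 3, and sample entropy and fALFF to Aim 3. All four come from fMRI runs. The Aim 3 section turns them into whole-brain maps for LASSO-PCR and then the deep Boltzmann machine, and takes the ROC curve from a randomly chosen part of the same cohort.

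**The concern.** Motion correction realigns volumes, scrubbing drops the worst volumes, and exclusion drops the worst scans. Retained participants can still differ in motion below those cut-offs and in how many usable volumes they contribute. If that residue differs between groups and is related to the outcome, the ANCOVA attributes it to group, because no term in the stated model represents it. The RRF covariate does not fill the gap: it measures cerebrovascular reactivity in a separate breath-holding run.

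For Aim 3, a group difference in motion would be present in both the model and the validation part of a random split. A classifier that partly reads motion could therefore still produce a good validation ROC. The protocol already reasons this way about other non-disease explanations: it adjusts HRF for cerebrovascular reactivity, and it uses sedentary controls and an activity covariate so that inactivity is not mistaken for illness. Motion is an explanation of the same kind and has no counterpart in the stated model.

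**Working it through.** **Step 1: is a motion term stated anywhere at group level?** Taking the abstract, Data analysis plan, Aim 1 section, Figure 4 legend and Controlling confounding factors together, the full set is activity, BMI, age, sex, depression and anxiety, plus the matching RRF feature for HRF. There is no motion measure. The protocol gives no figure for motion by group, so there is no plan figure to reproduce for the bias itself.

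**Step 2: illustrative size of the bias.**

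- From the protocol: 91 ME/CFS, 61 chronic fatigue, 91 HC and 45 fibromyalgia; 87% valid data; alpha 0.05.
- Assumed: the 13% loss is spread evenly over groups; residual motion in ME/CFS is *d* = 0.2, 0.3 or 0.5 SD above the other groups; the within-group correlation of motion with the outcome is *r* = 0.1 to 0.4. Both are taken as what remains after the planned covariates. There is no true group effect.

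Valid scans per group for ME/CFS and HC: 91 × 0.87 = 79.2.

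Spurious shift = *r* × *d*, from 0.1 × 0.2 = 0.02 SD to 0.4 × 0.5 = 0.20 SD.

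Standard error of the ME/CFS versus HC difference: √(2/79.2) = 0.159 SD.

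False-positive rate = Φ(δ − 1.96) + Φ(−δ − 1.96), with δ = *rd*/0.159. At the top corner δ = 0.20/0.159 = 1.26, which gives 24.2%. At the bottom corner δ = 0.02/0.159 = 0.13, which gives 5.2%.

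| *d* | *r* = 0.1 | *r* = 0.2 | *r* = 0.3 | *r* = 0.4 |
|---|---|---|---|---|
| 0.2 | 5.2% | 5.7% | 6.6% | 7.9% |
| 0.3 | 5.4% | 6.6% | 8.7% | 11.7% |
| 0.5 | 6.1% | 9.6% | 15.7% | 24.2% |

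For the planned four-group test, the noncentrality is λ = Σ n(μ − μ̄)². With only ME/CFS shifted, this is 79.2 × 171.4/250.6 × (*rd*)² = 54.2 × (*rd*)². It runs from 0.02 to 2.17, and the false-positive rate (noncentral F, 3 numerator df) from 5.1% to 20.3%. These are rates for one test before FDR correction.

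**Step 3: cost of one more covariate.** With power from the noncentral F, λ = N*f*² and denominator df = N − 4 − covariates, six covariates at N = 251 leave 241 df and seven leave 240. At *f* = 0.25 with 3 numerator df, power at N = 251 is 0.925 with six or with seven covariates, and the N required for 95% power is 279 either way. The plan's figure of 251 is reproduced with 2 numerator df, where power is 0.951 and is also unchanged by the extra covariate. That mismatch with a four-group test is a separate matter, and the motion point does not rest on it.

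**The case against.** The strongest case against has four parts.

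**Motion is already handled.** A reader might infer from the scrubbing and exclusion wording that nothing else is done. The protocol does not support that: the same sentence lists motion correction, and DTI has its own outlier replacement. What stands is narrower: all of this acts on images, and nothing at group level represents what remains.

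**No passage says that patients move more.** A reader might take the Actigraphy section's "changes after a moderate exertion (MRI scanning) in ME/CFS" as the sponsor's view that ME/CFS patients will move more in the scanner. That phrase gives the reason for studying sleep and heart rate variability after the scan and says nothing about head motion. The Figure 4 legend counts excessive motion for the sample as a whole, not by group. Motion arising from fatigue in general might also appear in the chronic fatigue and fibromyalgia groups. This objection stands in full: unequal motion is possible, not documented.

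**The covariate list may not be closed, and the full analysis plan is not shown.** Sex and RRF are themselves added outside the main list, and first-level motion regressors and scrubbing thresholds are properly left to a fuller plan; their absence here is not criticised. The article does, however, state a covariate set for all statistical analyses and builds its power analysis on the six subject-level ones. The point concerns that stated set.

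**Adjustment may remove real signal.** If motion is a consequence of illness, adjusting for it could understate a true difference. This is a fair reason not to make the adjusted result the only one, and it is met by showing both.

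**Conclusion.** The point holds as a gap in the stated group-level model. fMRI motion is corrected, scrubbed and, when excessive, excluded, but no motion summary is among the covariates. Residual motion that differs by group would be unadjusted in the HRF and RRF comparisons and could enter the neuromarker through four sets of maps, and the random split would not expose it.

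Its size is unknown. The range of about 5% to 24% for ME/CFS versus HC depends wholly on the assumed motion gap and correlation; at the low end the effect is negligible. The protocol supports neither a claim that a group difference in motion exists nor any particular inflation of the error rate. This is a low-cost improvement, not a flaw that invalidates the design.

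**What to change.** 1. Report mean framewise displacement by group, with the number of volumes kept after scrubbing, for the task and breath-holding runs. Displacement can be derived from the planned motion correction.
2. Present each fMRI-derived group comparison with and without mean framewise displacement as a covariate, taken from the run that produced the outcome (task run for HRF, breath-holding run for RRF). State beforehand which version is the main one.
3. For Aim 3, report the validation ROC of a model using only motion, age, sex and BMI beside that of the neuromarker.

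The cost is about 1 degree of freedom per model, with no material change in power, plus one benchmark model. The downside is that the adjusted estimate is conservative if motion is part of the illness, which is why both versions should be shown.

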#### Group difference in hemodynamic response function (HRF) (Aim 1)

The HRF features will be compared using one-way analysis of covariance (ANCOVA) among the four groups. The respiration response function (RRF) will be modeled in the breath-holding tfMRI data. This will enable us to disentangle non-neuronally-induced cerebrovascular reactivity from the neurovascular coupling effects. The RRF will be summarized similarly to the HRF by amplitude (*H*), time to peak (*T*), onset (*O*), and width (*W*). The RRF features at the same brain location will be used as a covariate in the HRF ANCOVA analysis to exclude confounding cerebrovascular reactivity (e.g., RRF-*H* as a covariate for HRF-*H* comparison, etc.,). Group differences in each RRF feature will also be tested using ANCOVA among the four groups. The bivariate correlation will be tested between the HRF/RRF features and the health scores. Additionally, the extent to which these correlated features explain variance in the health scores after accounting for all other variables will be evaluated using hierarchical regression.

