### The primary outcomes

#### Aim 1

To establish *group* differences in Hemodynamic Response Function (HRF) and its relationship to fatigue severity in ME/CFS patients using functional MRI (fMRI).

#### Aim 2

To establish *group* differences in dynamic glutamate activity during cognitive tasks and its relationship to fatigue severity in ME/CFS patients using functional magnetic resonance spectroscopy (fMRS).

#### Aim 3

To develop a neuromarker for ME/CFS diagnosis. The neuromarker will be relevant brain features integrated from multiple MRI modalities using a deep learning framework and validated using independent data.

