#### Group difference in dynamic glutamate response induced by cognitive task (Aim 2)

To directly test our hypothesis of an elevated dynamic glutamate response to cognitive tasks, dynamic glutamate response will be compared among the four groups using ANCOVA. In addition, dynamic glutamate response provides another measure of neural activity, which is considerably less sensitive to vascular changes. Establishing these differences will enable us to further elucidate NVC abnormality in ME/CFS. Bivariate correlations will be tested between the dynamic glutamate responses and health scores. In addition, the extent to which these correlated responses explain variance in the health scores after accounting for all other variables will be evaluated using hierarchical regression.

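### The severity part of Aims 1 and 2 starts with a bivariate correlation that carries none of the covariates required for all analyses, and on the natural reading this step selects what reaches the adjusted regression

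*Protocol article*

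**What the plan says.** Aims 1 and 2, listed under The primary outcomes, each have two parts: a group difference and a relationship to fatigue severity within ME/CFS patients. For Aim 2 the wording is "dynamic glutamate activity during cognitive tasks and its relationship to fatigue severity in ME/CFS patients"; Aim 1 says the same of the hemodynamic response function (HRF).

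The Data analysis plan sets a general rule: "The activity measure, body mass index, age, depression, and anxiety will be included as covariates for all statistical analyses". The Abstract states the same rule with sex in the list, and Controlling confounding factors adds: "We will include sex as a covariate in all statistical analyses". The full set is therefore six covariates.

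For the severity part, the Aim 1 section says: "The bivariate correlation will be tested between the HRF/RRF features and the health scores". The Aim 2 section says: "Bivariate correlations will be tested between the dynamic glutamate responses and health scores". Each section then plans a hierarchical regression. For Aim 1 it evaluates "the extent to which these correlated features explain variance in the health scores after accounting for all other variables"; Aim 2 has the parallel sentence for glutamate responses.

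On the respiration response function (RRF), the Aim 1 section says: "The RRF features at the same brain location will be used as a covariate in the HRF ANCOVA analysis to exclude confounding cerebrovascular reactivity". This sentence names the ANCOVA only.

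**The concern.** The general rule and the named severity test are incompatible. A correlation between two variables adjusts for nothing, so an analyst who follows the aim-specific sections breaks the general rule, and one who follows the general rule does not run the test that is named.

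The order of the steps matters too. The regression is described for features or responses that have been found correlated. Read naturally, the unadjusted step decides what is later examined with adjustment. Two things follow:

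- A correlation produced by age, body mass index or another covariate can be reported as a planned severity result.
- An association that a covariate masks may never reach the model that would reveal it.

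For HRF there is a further inconsistency. The group comparison removes the matching RRF feature so that the result reflects neurovascular coupling rather than vascular reactivity, and Disentangling NVC gives the same rationale. The severity correlation leaves RRF in, so the two halves of Aim 1 describe different quantities. This does not concern Aim 2.

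**Working it through.** The article gives no figure for the severity analysis, so there is none to reproduce. The conflict itself needs no arithmetic. The calculation below sizes its consequences.

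**Inputs from the article**
- ME/CFS patients: 91 (recruitment section). Valid data: 87% (Figure 4 legend). 91 × 0.87 = 79.2, so n = 79.
- Type I error 0.05 (Figure 4 legend), taken as two-sided per test, before FDR.

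**Assumptions (no correlations are given)**
- One covariate, or RRF, correlates *a* with the imaging feature and *b* with the health score. I take the health score as the severity measure.

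**Formulas**
- Bivariate r = partial r × √((1 − a²)(1 − b²)) + a·b. With a partial r of 0 this is a·b.
- Test statistic mean = atanh(r) × √(n − 3); √76 = 8.718. Significant if beyond ±1.96.

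**(a) No true adjusted association (partial r = 0), n = 79**

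| a | b | bivariate r | mean z | significant at the bivariate step |
|---|---|---|---|---|
| 0 | 0 | 0 | 0 | 5% |
| 0.3 | 0.3 | 0.09 | 0.79 | 12% |
| 0.5 | 0.3 | 0.15 | 1.32 | 26% |
| 0.7 | 0.3 | 0.21 | 1.86 | 46% |

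If all valid participants were pooled (n = 251), r = 0.09 and 0.15 would be significant 30% and 66% of the time.

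Simulating both steps at n = 79 (bivariate test, then adjusted test) for the three confounded rows, a null feature passes both in about 2.4% to 2.9% of runs. The adjusted test alone rejects in about 5%.

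**(b) True partial r = 0.30, covariate acting in the opposite direction, n = 79**
- a = 0.3, b = −0.3: r = 0.30 × 0.91 − 0.09 = 0.183; mean z 1.61; passes 37%.
- a = 0.4, b = −0.4: r = 0.30 × 0.84 − 0.16 = 0.092; mean z 0.80; passes 13%.
- Adjusted test: atanh(0.30) × √76 = 0.3095 × 8.718 = 2.70, power 77%. With six covariates, 0.3095 × √70 = 2.59, power 74%.

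**(c) True partial r = 0.30, covariate acting in the same direction, n = 79**
- a = b = 0.3: r = 0.273 + 0.09 = 0.363. The bivariate step passes about 92% in simulation. Both steps together keep 77%, the same as the adjusted test alone, so nothing is lost.

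**The case against.** The strongest reply is that an adjusted severity analysis is already planned. The bivariate correlation is the first of two steps, and showing unadjusted and then adjusted associations is a familiar and defensible sequence. This stands in part. A reader might infer from the 12% to 46% in (a) that the study's final severity findings carry inflated false-positive rates. They do not: those figures belong to the first step alone, and passing both steps is rarer than 5%.

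Second, the gate is inferred. No threshold or exclusion rule is stated, so the text does not prove that uncorrelated features are left out of the regression. This is fair, but the wording confines the regression to correlated features and offers no other route into it.

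Third, a reader might infer that the plan requires RRF to be removed from HRF wherever HRF is used. It does not. The RRF adjustment is written for the HRF ANCOVA, and the regression's remaining variables may include RRF. Its absence from the correlation is at odds with the stated rationale but breaks no explicit rule.

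Fourth, the sizes rest on assumed correlations and are before FDR. With links of 0.1 and 0.1 the bivariate rejection rate stays near 5%, and loss at the first step needs an opposing covariate. Both limits are accepted.

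None of this reconciles the general covariate rule with a named test that cannot carry covariates.

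**Conclusion.** The concern holds in a limited form. The article requires covariates in all statistical analyses and then names a covariate-free test as the first severity analysis in primary Aims 1 and 2. That contradiction is in the text and depends on no assumption.

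The consequences are two. Confounded correlations would count as planned severity tests: 12% to 46% significant under a true null at n = 79, for assumed links of 0.3 to 0.7 with the feature and 0.3 with severity, before FDR. And, if the first step acts as a screen, real associations opposed by a covariate can be lost: 37% to 13% pass, against about 77% for an adjusted test, for assumed opposing links of 0.3 to 0.4. There is no loss when the covariate acts in the same direction.

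The documents do not support the stronger conclusions that the severity analysis is wholly unadjusted or that its final error rate is inflated. The RRF inconsistency is confined to HRF in Aim 1. The point merits correction before the final analysis; it does not undermine the group comparisons.

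**What to change.** In the Aim 1 and Aim 2 analysis sections, make the covariate-adjusted association the severity test for every predefined feature, whatever its bivariate result:

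- Use a partial correlation or regression coefficient within ME/CFS patients, with one model per feature.
- Include the full covariate set: activity, body mass index, age, sex, depression and anxiety. For each HRF feature in Aim 1, add the matching RRF feature.
- Apply FDR to these adjusted tests.
- Keep the bivariate correlations as descriptive output.

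The change uses data already being collected. Each model spends six degrees of freedom, or seven for HRF, out of about 79. For a partial correlation of 0.30 that lowers power from 77% to about 74% with six covariates, or 73% with seven (0.3095 × √69 = 2.57). Patients without a valid breath-hold run drop out of the HRF models, as they already do in the HRF ANCOVA.

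The main drawback is interpretive. Activity, depression and anxiety may be partly consequences of severity; the recruitment section itself attributes patients' reduced activity to the illness. Adjusting for them may remove part of the association of interest. A sensitivity analysis with age, sex and body mass index only (plus RRF for HRF) can be shown alongside.

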#### Neuromarker identification and validation (Aim 3)

The data will be randomly divided into a model group (168 samples from 51 ME/CFS, 41 fatigue conditions, 51 HCs, and 25 fibromyalgia), as well as a validation group (120 samples from 40 ME/CFS, 20 fatigue conditions, 40 HCs, and 20 fibromyalgia). The region-based HRF features, RRF features, sample entropy, and fractional amplitude of low-frequency fluctuations will be converted into whole-brain voxel-wise maps by assigning regional measures to each voxel within the region and zeros outside. Each MRI measure (GM and WM density map, HRF features, etc.) will be entered as input for least absolute shrinkage and selection operator—regularized principal components regression (LASSO-PCR) (21) to generate a brain pattern of distributed clusters that predict disease severity. The identified brain pattern will be integrated using multimodal deep Boltzmann machines (DBM) (22) as a neuromarker to predict ME/CFS. The importance of each cluster in the brain pattern will be determined by the Kullback-Leibler divergence of the prediction distributions with and without it. Clusters with no significant information gain will be removed. The receiver operating characteristic (ROC) curve of the identified neuromarker will be determined using data from the validation group.

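### In Aim 1, and to a smaller degree Aim 2, predictors are chosen by their correlation with a health score and then assessed for variance explained in the same people, so the R-squared increment is biased upward

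*Protocol article*

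**What the plan says.** Under the Aim 1 analysis heading, the protocol article first states: "The bivariate correlation will be tested between the HRF/RRF features and the health scores". A hierarchical regression then evaluates "the extent to which these correlated features explain variance in the health scores after accounting for all other variables". The Aim 2 analysis section has the same two steps, ending in "the extent to which these correlated responses explain variance in the health scores after accounting for all other variables".

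The general part of the data analysis plan adds: "The false discovery rate (FDR) will be used to correct for multiple comparisons". It gives no FDR level.

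The response curves are summarised by four parameters each (amplitude, time to peak, onset, width), giving eight feature types per location. The Aim 3 section describes these features as region-based, but the number of regions is not stated. The only division into model and validation data is in the Aim 3 section.

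**The concern.** The most natural reading is that the features entered are those found to correlate with the score. A feature passes when its sample correlation is large, which happens partly because its true correlation is large and partly by chance. The regression, run in the same people, counts the chance part as variance explained. Its F test takes the predictors as fixed in advance, which they are not.

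The relationship to fatigue severity is the second half of primary Aims 1 and 2, and this increment in R-squared is its quantitative answer. Readers could take it as the share of severity that neurovascular coupling explains, and take its p-value as a second confirmation of the correlation.

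**Working it through.** **The plan's own figure.** There is none to reproduce: the power analysis covers only the group comparison.

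**Inputs from the article.** There are 91 ME/CFS patients and 87% of data are expected to be valid, so 91 × 0.87 ≈ 79. All groups together give 251 valid. There are 4 + 4 = 8 feature types per location. The power analysis lists six covariates by name.

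**Assumed.** FDR level 0.05 (Benjamini–Hochberg); 1 to 800 candidate features; n = 79 if the analysis is confined to ME/CFS, 251 if it pools all groups.

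**Step 1: the floor that selection imposes.** A feature passing alone among m candidates needs p ≤ 0.05/m, so its sample r² is at least t²/(n − 2 + t²), whatever the truth.
- n = 79, m = 1: t = 1.991, so 3.964/80.964 = 4.9%.
- n = 79, m = 8: t = 2.812, so 7.907/84.907 = 9.3%.
- n = 251, m = 1: t = 1.970, so 3.880/252.880 = 1.5%.
- n = 251, m = 8: t = 2.758, so 7.607/256.607 = 3.0%.

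This is the bivariate r². After covariates that predict the score, the increment can be lower, so the two steps were simulated.

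**Step 2: simulation with true effects.** Independent features, FDR screen, then regression on six covariates (explaining 30% of the score) plus the selected features. Two of 8 or four of 80 features carry a true correlation r. Entries are the mean reported increment against the true R-squared of the same selected features, among data sets where something passed.

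| n | r | 8 features | 80 features |
|---|---|---|---|
| 79 | 0.15 | 0.085 vs 0.021 (4.0×) | 0.105 vs 0.016 (6.6×) |
| 79 | 0.20 | 0.104 vs 0.043 (2.4×) | 0.123 vs 0.036 (3.4×) |
| 79 | 0.30 | 0.169 vs 0.129 (1.3×) | 0.214 vs 0.149 (1.4×) |
| 251 | 0.15 | 0.049 vs 0.029 (1.7×) | 0.068 vs 0.032 (2.1×) |
| 251 | 0.20 | 0.078 vs 0.064 (1.2×) | 0.120 vs 0.090 (1.3×) |
| 251 | 0.30 | 0.179 vs 0.178 (1.0×) | 0.348 vs 0.348 (1.0×) |

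With 800 features and n = 251: 0.064 vs 0.022 (2.9×) at r = 0.15, and 0.102 vs 0.063 (1.6×) at r = 0.20.

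**Step 3: other assumptions.**
- n = 79, features correlated 0.3 with each other, one of 8 explaining 5%: 13.5% vs 4.3% if the covariates are unrelated to the score, 10.4% vs 4.3% if they explain 30% of it.
- Same, one of 40 explaining 4%: 18.5% vs 2.6%, and 11.6% vs 2.3%.
- Same, four of 100 jointly explaining 10%: 27% vs 5.7%, and 19.9% vs 5.5%.
- n = 251, 100 features, four jointly explaining 5%, covariates unrelated to the score: 11.4% vs 3.3% (3.5×).
- A single feature, the case nearest to Aim 2: 7.2% vs 4.0% at n = 79 (1.8×), and 4.4% vs 4.0% at n = 251 (1.1×).

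**Step 4: no true association** (covariates unrelated to the features). About 5% of data sets pass the FDR screen. Among those, for 1/8/80/800 features:
- n = 79: mean increment 0.034/0.060/0.083/0.113; F test significant in 44/79/94/99%.
- n = 251: mean increment 0.012/0.020/0.029/0.040; F test significant in 49/85/95/100%.

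**Step 5: after repair.** Selecting in one half and estimating in the other, with no true association, brings the adjusted increment to −0.003 to 0.002. The F test is then significant in about 1–7%, wherever enough runs had a selection.

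**The case against.** **FDR control is planned.** About 95% of analyses with no true association never reach the regression. That stands, and it protects against false discoveries. It does not correct the estimate for features that pass, which is the quantity the regression is there to report.

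**The regression adjusts for other variables, so it does real work.** This also stands in part. Suppose a bivariate correlation arises only because a covariate drives both feature and score (assumed: it explains 30% of the score and correlates 0.4 with each feature). The F test was then significant in about 1–6% of screened data sets with 1, 8 or 40 features. That reassurance weakens with many otherwise independent features in 79 patients.

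**A reader might infer that the increment is inflated several-fold whatever the setting, and that its test is almost always significant.** The documents do not support either. Number of regions, correlation among features, FDR level and analysis population are not given. The inflation is near 1 for r = 0.30 at n = 251. The high significance rates are conditional on passing the screen.

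**A reader might extend the same size to Aim 2.** Spectroscopy uses one voxel, so there are one or few glutamate responses. With a single null response, roughly 5% pass and 44–49% of those are significant, about 2% overall.

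**The wording may mean only the features examined, with entry rules in a fuller plan.** This is possible, since no entry threshold is stated. But selection is the more natural reading, and the two-step order is fixed in the article itself.

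**Conclusion.** The point holds for Aim 1 and, to a much smaller degree, for Aim 2. As written, the increment in R-squared is biased upward and its nominal F test is not valid as independent confirmation.

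The size can only be given under assumptions. It is roughly 2- to 7-fold for weak effects with about 79 valid ME/CFS patients and 8 to 100 features. It is about 1.0- to 2-fold in most cases with 251 participants and 8 to 80 features, and more with 100 or above. For a single glutamate response it is modest.

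After selection the F test rejects in about 45–100% of null data sets when covariates are unrelated to the features, rising with the number of features. It stays near nominal in most of the cases examined where the correlation runs through the covariates. This deserves correction, but it does not touch the group comparisons or the Aim 3 validation.

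**What to change.** **Aim 1 analysis section.** Choose one of two wordings.
1. Enter a feature set fixed without looking at the correlations, for example one named response parameter and its matched respiration counterpart in named regions. The F test for that set then keeps its usual meaning.
2. Keep the screen, but repeat screen plus regression inside each cross-validation fold or bootstrap resample, and report the optimism-corrected increment in R-squared. The FDR-adjusted correlation is then the test, and the post-screen regression p-value is not quoted as a separate one.

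**Aim 2 analysis section.** Enter the glutamate response in the regression whether or not its bivariate correlation is significant.

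**Cost.** A change of wording and a little more computing, with no new data. The reported variance explained will be smaller and its interval wider.
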